	**Strategy 1: Clinician implementation team meetings**
Actor(s)	The team of clinicians who are implementing the NM Bridges intervention
Action(s)	Reflect on the implementation effort, share lessons learned, support learning, and propose changes to be implemented in small cycles of change.
Target(s) of the action	Clinicians newly trained in the intervention.
	Knowledge about how to use the intervention in this context, intentions to use the innovation, social influences.
Temporality	First meeting should be within two weeks of initial training.
Dose	Once monthly for 1 h for the duration of the trial.
Implementation outcome(s) affected	Uptake of the intervention, penetration among eligible clients/patients, fidelity to the protocol of the clinical innovation, sustainability of the innovation.
Justification	Cooperative learning theory [63]
	**Strategy 2: NM Bridges “champion” (develop stakeholder interrelationships)**
Actor(s)	Individual clinician in the clinical setting
Action(s)	Facilitating reflection; serving as team leader; motivating staff; engaging in planning activities; persuading staff that the initiative was important and worthwhile; building relationships with key stakeholders; using data to persuade peers
Target(s) of the action	Clinician newly trained in the intervention
Temporality	Ongoing input throughout trial, MDT meetings, flexibility to respond and tailor as appropriate
Dose	Ongoing input throughout trial
Implementation outcome(s) affected	Uptake of the innovation, fidelity to the protocol of the clinical innovation, acceptability to clinicians.
Justification	Advocacy for clinical champions with literature [57, 60, 64]
	**Strategy 3: Adapt and tailor to context**
Actor(s)	Intervention development team
Action(s)	Conduct co-design activities to tailor NM Bridges training to clinical setting and population
Target(s) of the action	Clinicians newly trained in the intervention
	Knowledge about how to use the intervention in this context, intentions to use the innovation, social influences.
Temporality	Co-design sessions to take place 1 month prior to delivery of training, allowing time for appropriate modification of training and materials
Dose	2 co-design sessions prior to staff training in intervention
Implementation outcome(s) affected	Uptake of the intervention, penetration among eligible clients/patients, acceptability to clinicians, fidelity to the protocol of the intervention, appropriateness of intervention to context
Justification	Research suggests that tailoring interventions to a particular context has positive effect on healthcare outcomes [61, 65]
	**Strategy 4: Educational materials**
Actor(s)	Local opinion leaders (key members of clinical team)
Action(s)	Email provision of NM Bridges resources, links to Bridges webinars, supporting literature, examples of successful use of intervention to include patient success stories
Target(s) of the action	Clinicians newly trained in the intervention
	Knowledge about how to use the intervention in this context, intentions to use the innovation
Temporality	First educational email within 2 weeks of start of trial
Dose	Weekly email to provide updates, encouragement, and feedback on intervention implementation
Implementation outcome(s) affected	Uptake of the intervention, acceptability to clinicians, fidelity to protocol
Justification	Theoretical Domains Framework (Reinforcement, environmental context & resources, social influences) [66]

#### Fidelity

Fidelity of NM Bridges will be assessed through ten session observations by the research team, a self-reported fidelity checklist to be completed by clinicians after each session, and educational meetings/discussions. Ten intervention sessions will be video recorded and reviewed by the research team, who will evaluate the session against pre-determined fidelity markers. Sessions for observation/recording will be selected at random. All session observations and recordings will only take place with the informed consent of both the patient and clinician.

### Outcomes

#### Feasibility of the clinical intervention

Outcome measures related to the intervention will be completed at baseline, directly after receiving the intervention and 3 months afterwards. There will be the option for outcome measures to be completed remotely, for participant convenience, and to reduce risk associated with the COVID-19 pandemic. The outcome measures will focus on the intervention’s impact on health-related quality of life (EQ-5D [67]), self-efficacy (GSES [68]), mood [General Health Questionnaire (GHQ [69])], and participation (Ox-PAQ [70]). A profile of the broad impacts of the intervention will be measured through the Health Education Impact Questionnaire (heiQ) [71], which covers areas that patients, clinicians, policymakers, and researchers regard as important outcomes of patient education programs for people with long-term conditions. The person-centredness of the intervention will be measured through the Client-Centred Care Questionnaire [72], and the and Patient Assessment of Chronic Illness Care (PACIC) [73].

It is recommended that patient engagement is considered in the selection of outcome measurements [74], and as such, the outcome measures were selected based upon discussion with the project’s PPI group, who emphasised the need to consider the biopsychosocial impact of NMD, not just the physical elements. Once the views of people with lived experience of NMD had been obtained, measures were selected based on literature providing recommendations on the use of outcome measures for self-management interventions [22, 75], rare neurological conditions [76], and person-centred care [77, 78].

#### Feasibility of implementation

As recommended by the ImpRes framework [56], and Proctor et al. [79], a clear mechanism for measuring the effect of the implementation strategies on pre-defined implementation outcomes has been established. A mixed methods approach will also be employed for this aspect of the study. Quantitative measures were chosen from the Implementation Outcome Repository, based on a systematic review by Khadjesari et al. [80]. These will include (a) the Acceptability of Intervention Measure (AIM) [81], (b) Intervention Appropriateness Measure (IAM) [81], and (c) Feasibility of Intervention Measure (FIM) [81] which are four-item measures of implementation outcomes that are often considered “leading indicators” of implementation success [79]. We will also use the NoMAD scale [82, 83] which is a pragmatic, psychometrically tested instrument that measures implementation activities related to NPT. Table 4 describes the theoretical basis and techniques that will be used to measure the impact of the main implementation strategies on implementation outcomes.

Qualitative methods will be employed concurrently to gain a deeper insight into the opinions, thoughts, and feelings on NM Bridges of participants. Ten patients will be recruited for semi-structured interviews to explore their experiences of receiving NM Bridges. Six staff will be interviewed at the end of the intervention phase to investigate determinants of implementation behaviour and explore experiences of delivering NM Bridges. Ten patients is a pragmatic number in terms of funding, staffing, and time frame as this study forms part of a PhD project. There will be six staff interviews as this is how many staff members have been trained in the approach and subsequently delivering the intervention. The topic guide for patients has been informed by previous qualitative work into patient perspectives on self-management [84]. The topic guide for clinicians has been designed by mapping questions to the four constructs of NPT. Interviews will be audio recorded and transcribed by an external service, and a reflexive thematic analysis undertaken [85].

### Planned sample size and analyses

A target sample of 60 people with NMD will be recruited through the clinical service and neurology clinics at the Centre for Neuromuscular Diseases. A sample size of at least 30 is recommended for early feasibility studies, but a larger target has been set to account for potential dropouts and for secondary exploration of the performance and suitability of the outcome measures. We will collect data on screening, recruitment, and drop out reasons for all participants. The recruitment rate will be calculated from the total number of participants recruited over the recruitment window. This will be expressed as numbers recruited per month. Descriptive statistics will be used to describe averages at baseline and following the intervention. Continuous data will be presented as a mean, with standard deviation or median and interquartile range, as appropriate. For categorical/ordinal data, we will calculate frequencies and percentages. The effect of the intervention will be explored by calculating the adjusted Cohen’s *d* effect size statistic for continuous outcome measures or the adjusted Hedge’s G for ordinal outcomes [86].

Qualitative data in the form of semi-structured interviews will be audio recorded and transcribed verbatim and a reflexive thematic analysis will be conducted. The transcripts will be entered into the qualitative software management programme NVivo V.12, to facilitate data management. The qualitative analysis will be conducted by one researcher (LL) and discussed/reflected in the wider group of researchers and with the PPI advisory group (peer review). There is also a plan for independent double-coding of data.

The principal analysis approach will be deductive, answering to the aims of interviewing, i.e. to explore the participants’ experiences of the intervention and the experiences of staff delivering the intervention, with the possibility for inductive development of any further codes/themes should these be identified. There will be an assessment in how far qualitative findings match the results from quantitative measures (intervention outcomes, implementation measures). Qualitative findings will directly inform design decisions of the intervention and implementation strategies for a follow-on study.

In terms of success criteria, the study findings will be assessed and judged in context, i.e. recruitment rate in relation to patient volume of the service, and intervention effect by comparison with other positive trials of self-management interventions in other clinical populations.

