### Study design

We will be using an embedded experimental mixed methods design, to address the research questions, as this is an often used design when evaluating health services research [31]. An embedded design, where one data set provides a supportive secondary role to the other, is frequently used when researchers need to include a qualitative component within a quantitative study. The use of qualitative methods post-intervention will enable us to follow up on the participants’ experiences of the intervention, and the experiences of staff delivering the intervention [32]. This approach will enable us to gain an understanding of how the intervention fits in with the day to day workings of the clinical centre, the perceived value it provides to patients, and provide data on potential barriers and facilitators to the uptake of the intervention [33].

The feasibility of the intervention will be tested through a single-arm pre-post design, with participants completing outcome measures before, directly after, and 3 months post-intervention. A randomised control trial, which is a higher design in the traditional hierarchy of evidence, was considered for this work. However, it was felt that randomisation at the patient level could be problematic due to the potential for intervention contamination when clinicians are transitioning back and forth between providing (a) routine care or (b) the intervention, for different patients.

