It is now widely accepted that addressing the challenge of implementing evidence-based interventions into routine practice is of fundamental importance to the global health community, and implementation science is regarded as a vital tool in closing the evidence-to-practice gap [20]. The consideration of implementation components in research is not new. For example, Bowen et al. [34] recommend employing feasibility studies to study general areas such as acceptability, adaptation, and demand, which clearly have overlap with established implementation outcomes. However, a consideration for implementation components in feasibility studies is not always reflected in the literature. In this study, we propose using a hybrid methodology to permit a dual focus on both feasibility testing of the intervention, and feasibility testing of the implementation strategy package. It is hypothesised that this design, will allow us to interrogate the implementation aspects of this trial in a more structured, coherent, and rigorous way, whilst simultaneously gathering valuable data on the clinical intervention. At the end of the study, we will reflect on the value of using this approach at the feasibility stage for future implementation studies.

Feasibility data from this study will be used to inform future implementation efforts in the form of a cluster randomised study, as ultimately implementation questions would benefit from more sites to include different systems and infrastructure, to address potential limits on generalisability. Prior to setting this up, there will be scoping work required at potential sites to understand the nuances of delivery that may differ. This will allow us to collaboratively design the trial with the partner sites to explore the implementation and ensure fidelity within the different contexts. This exploratory study will provide information for us to refine delivery of the intervention at “treating” sites, for comparison with control sites where usual treatment will be provided. We are aware that there are limitations of the pre-post design and that missing information would need to be substituted/estimated from other available studies; or estimated from data collected later on, for example during an internal pilot phase of a definitive cluster RCT.

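### One of the two success criteria compares an uncontrolled before-after change with positive trials in other populations, a comparison that cannot be interpreted in either direction

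*Protocol article*

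**What the plan says.** Under Planned sample size and analyses, the Protocol article says findings will be judged in context and gives two success criteria. The first is "recruitment rate in relation to patient volume of the service". The second is "intervention effect by comparison with other positive trials of self-management interventions in other clinical populations".

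The design that must supply the second is set out under Study design: "The feasibility of the intervention will be tested through a single-arm pre-post design", with "participants completing outcome measures before, directly after, and 3 months post-intervention". There is no control group. The analysis text nevertheless presents the standardised change as an effect of the programme: "The effect of the intervention will be explored by calculating the adjusted" Cohen's d, or Hedges' g for ordinal outcomes. The target is 60 participants.

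The article does carry a general caveat under Study design: "We are aware that there are limitations of the pre-post design". It adds that missing information would have to come from other studies or from a later internal pilot phase. That caveat is not tied to the success criteria.

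**The concern.** The criterion needs two things: an estimate of what NM Bridges does, and a fair yardstick to set it against. The plan supplies neither.

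- **The estimate.** Without a control, the change from baseline is the programme's effect plus whatever would have happened anyway. The Introduction describes many of these diseases as progressive, so decline is plausible. Regression to the mean and non-specific response to being seen and asked could push the other way.
- **The yardstick.** The comparators are chosen on their result. Averages taken over trials selected for being positive tend to exceed the true effect in those trials.
- **The match.** The comparators come from other clinical populations, and the article itself explains why its own population and delivery differ.

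At stake is how the study is read when it informs the later cluster randomised study. A statement that the effect did or did not match positive trials elsewhere would look like evidence about NM Bridges, but would not be.

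**Working it through.** The plan gives no figure for this criterion: no comparator trial, threshold or margin. There is therefore nothing to reproduce. The numbers below are illustrations under stated assumptions, followed by a comparison of the article's own passages.

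**1. Benchmark built from positive trials.** Assumptions: the comparators are two-arm trials with n per arm, positive means significant in the favourable direction at two-sided 5%, and d is approximately normal.

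SE = √(2/n); z = 1.96 − d/SE; mean d among significant trials = d + SE × φ(z)/(1 − Φ(z)).

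Worked case, d = 0.30 and n = 50: SE = √(2/50) = 0.20; z = 1.96 − 1.50 = 0.46; power 1 − Φ(0.46) = 0.323; φ(0.46) = 0.359; mean = 0.30 + 0.20 × 0.359/0.323 = 0.52.

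| True d | n per arm | Power | Mean d if significant | Ratio to truth |
|---|---|---|---|---|
| 0.30 | 30 | 0.21 | 0.65 | 2.18 |
| 0.30 | 50 | 0.32 | 0.52 | 1.74 |
| 0.30 | 100 | 0.56 | 0.40 | 1.33 |
| 0.30 | 200 | 0.85 | 0.33 | 1.09 |
| 0.50 | 30 | 0.49 | 0.71 | 1.42 |
| 0.50 | 100 | 0.94 | 0.52 | 1.03 |
| 0.50 | 200 | 0.999 | 0.50 | 1.00 |

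The overstatement is large for small trials and close to nil for well-powered ones. The article does not say which kind would be used.

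**2. What the single arm observes.** Before-after d = programme effect + non-specific change. Assume a non-specific change between −0.2 and +0.2 SD (not in the documents).

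- True effect 0.30: observed d runs from 0.30 − 0.20 = 0.10 to 0.30 + 0.20 = 0.50.
- True effect 0: observed d runs from −0.20 to +0.20.

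**3. Putting 1 and 2 together.** Take a true effect of 0.30 both here and in the comparators. Against a benchmark of 0.33 (200 per arm), an observed 0.50 exceeds it and an observed 0.10 falls short. Against 0.52 (50 per arm), even 0.50 falls just short. The reading follows from the unknown non-specific change and the unknown size of the comparator trials, with the programme's effect held fixed throughout.

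**4. Sampling error is a separate matter.** With the baseline SD as standardiser and pre-post correlation r (assumed), SE = √(2(1 − r)/n + d²/(2n)). At n = 60, r = 0.7, d = 0.3: √(0.010 + 0.00075) = 0.104, so the 95% half-width is 1.96 × 0.104 = 0.20. Over r = 0.8 to 0.5 it is 0.17 to 0.26 at n = 60, and 0.24 to 0.37 at n = 30. Such an interval describes the precision of the change. It does not remove the non-specific part.

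**5. The article against itself on comparability.**

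- The Introduction contrasts neuromuscular disease with stroke and traumatic brain injury, which it describes as relatively stable after a single onset.
- The section on the NM Bridges intervention says earlier Bridges studies delivered the programme over a series of rehabilitation sessions, whereas here it is a one-off session.
- The success criteria then take other populations as the yardstick, with no allowance for either difference.

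**The case against.** The strongest reply is that the sentence is soft. Findings are to be judged in context, effects are only to be explored, and the Objectives list acceptability, demand, performance of measures, recruitment, retention, fidelity and adoption, not clinical effectiveness. The pre-post limitation is acknowledged, and no threshold or stopping decision hangs on the effect. This stands as a limit on the consequences. It does not remove the criterion: effect is one of only two things named as success, and the general caveat never qualifies it.

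A second reply is that a fuller protocol or SAP may fill the gap. It could name the measure, the time point and the comparator trials. It could not supply a control group, and while comparators are chosen for being positive the benchmark remains selected on its result.

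Three stronger readings are tempting, and the documents do not support them.

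- A reader might infer that a useless programme could be declared a success on the best of several measures and time points. The article states no such pass rule and no cut-off, so a false-success probability would rest on invented inputs. Which measure counts is a detail an article may leave to the SAP.
- A reader might infer a formal go/no-go decision on effect. None is stated; the data are to inform later work.
- A reader might infer that the comparators report between-group effects, so that two different quantities are certainly being compared. The article does not give their design. If they were themselves uncontrolled, the selection and population problems would remain.

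**Conclusion.** The criterion is wrong as written. A single-arm before-after change does not estimate the effect of NM Bridges, the benchmark is selected on its result, and the article itself says that disease course and delivery differ.

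The size of the benchmark's overstatement cannot be derived from the documents. Under the assumptions above, at a true d of 0.30, it runs from about 9% (200 per arm) to more than double (30 per arm), and it is near nil where comparators are well powered.

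The net direction is undetermined. An inflated benchmark or disease progression makes success look harder to reach; regression to the mean or non-specific improvement makes it look easier. The defect is therefore that the comparison is uninterpretable. A bias towards success or towards failure is not shown.

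This is a correction to the wording of the success criteria. It gives no reason to change the design, the sample size or the data collected.

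**What to change.** 1. Delete intervention effect from the success criteria under Planned sample size and analyses.
2. Judge success on the feasibility objectives that the article already lists and plans to measure: recruitment, retention, data completeness, fidelity and acceptability.
3. Keep the before-after changes, each with a 95% confidence interval, as description only. State beside them that they do not estimate the effect of NM Bridges. If results from other populations are mentioned, put them in the discussion as background and do not restrict them to positive trials.

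The cost is a few sentences and no new data. The downside is that the study can no longer claim success on effect, a claim this design could not have supported.

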### Dissemination

We will use a range of approaches to disseminate our findings. The results and analysis of the study will be disseminated to service users through publication and on the Muscular Dystrophy UK (MDUK) website. MDUK is the main charity for people with muscle wasting conditions in the UK. The study findings will also be disseminated to the other major NMD charities to share with their members and followers. The research team will be disseminating the results of the study through videoblogging on social media, to make the findings more accessible to individuals who prefer to interact using these platforms. Academic dissemination will include publications and presentations to researchers and healthcare professionals, and there will be an emphasis on service-user collaboration and public engagement in dissemination strategies. We will also work with the team at the specialist centre to develop strategies for disseminating findings and meet with them to discuss the study’s implications and next steps.

## Data Availability

Not applicable.
